### Data collection and data analysis

2.7

#### Data collection

2.7.1

All clinical data will be collected in the clinical report form (paper CRF). These data will be entered anonymously into a computerized database using REDCap (Research Electronic Data Capture) (59), a web application for building and managing research databases. The use of a dedicated tool is suitable for robust data collection, data quality checks, and limiting missing data. All the users will have private access to the database with personal credentials and dedicated roles. Each patient will be associated with a reference ID and the correspondence between the patient’s name and the associated ID will be stored in a secure external file, to which only clinicians involved in patients’ assessment will have access.

Instrumental data on postural sway and gait analysis will be stored in a computer with restricted access for the personnel dedicated to the analysis of these data. Gait parameters collected using C-Mill in C-Gait mode will be stored in the computer connected to the C-Mill system, which also has restricted access to the staff involved. Biological samples collected at IRCCS Don Carlo Gnocchi in Florence will be sent for analysis, after anonymization, to the LABION at IRCCS Fondazione Don Carlo Gnocchi in Milan.

#### Data analysis

2.7.2

Statistical analysis will be conducted using the software SPSS v28 (Armonk, NY: IBM Corp). The distribution will be assessed using the Kolmogorov–Smirnov test for all clinical and instrumental continuous data, assuming the presence of normal distribution when *p* > 0.05. Data will then be summarized as mean and standard deviation, median and interquartile range, or absolute and percentage frequency, as appropriate.

The experimental and the control groups will be compared at baseline to explore significant differences in demographic, clinical, and instrumental variables. Parametric or non-parametric tests will be used for continuous variables, according to data distribution. The chi-square test will be used to compare distributions of binary/categorical variables.

Both within and between-group analyses will be conducted to assess at each time point the effects of the treatments delivered, for primary and secondary outcome measures. Specifically, a two-way repeated measures ANOVA will be used with a within-factor (time of assessment) and a between-factor (group).

Regarding biological data, the acquired Raman spectra will be analyzed by multivariate Principal Component Analysis – Linear Discriminant Analysis (PCA-LDA) classification. PCA will reduce the number of variables into principal components, which will be used to build the LDA model. The model will be built to discriminate clinical improvement detected as quantifiable change on clinical scales, defined based on the minimum clinically important difference, when available from the literature. The sensitivity, specificity, and accuracy of the predicting model based on spectra data will be assessed. In addition, correlation analysis will be conducted to evaluate the association between spectral data and change on clinical scales recorded between the treatment’s beginning and end. Statistical analysis of the Raman data will be performed using Origin2023b (OriginLab Corporation, Northampton, MA, USA) (34).

Univariate analysis models will be used to select the best prognostic markers of clinical improvement to be included in a multivariate model.

For all analyses, statistical significance will be set at *p* < 0.05.

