### Study design

2.1

This is a single-center, no-profit, parallel arm randomized controlled single-blind trial with an active comparator where the experimental intervention is represented by an TT+AVR and the comparator by a conventional TT.

Randomization will be performed by an external Researcher (not involved in the study design or procedures): a list of 0–1 will be generated using Phyton. Allocation will be concealed. Medical staff will propose consecutively the study for all eligible patients referring to the Parkinson Unit and the IRCCS Don Gnocchi Florence, assigning, in case of enrollment, an identification number to the participant.

Outcome raters will be blinded to the treatment assignment, including clinicians assessing the eligibility of patients and the raters (Neurologist, Physiatrist, Psychologist, Physiotherapist, Laboratory staff). Blindness will be ensured by the modality and timing of assessments at T0, T1, and T2 that will be conducted at times other than treatment and by raters not involved in the training. Blinding will be removed if requested by the participant at the end of the study and in case of undesirable effects.

The promoter of the study is the Department of Clinical and Experimental Medicine, University of Florence, Italy; the study will be performed at “Struttura Organizzativa Dipartimentale (SOD) di Riabilitazione Generale-Istituto di Ricovero e Cura a Carattere Scientifico (IRCCS) Fondazione Don Carlo Gnocchi, Florence.”

Two collaborators for external services will take part in the study:

The Movement Analysis Laboratory at IRCCS Don Carlo Gnocchi Florence, dedicated to instrumental data analysis (postural sway and gait analysis).The Laboratory of Nanomedicine and Clinical Biophotonics (LABION) at IRCCS Fondazione Don Carlo Gnocchi, in Milan, dedicated to biological data analysis.

The study received Ethical Committee approval from the local Institutional Review Board (Comitato Etico Regione Toscana – Area Vasta Centro) on the 5th of July 2022 (Approval Number: 20915_spe).

The registration on ClinicalTrials.gov has been completed and the study has been reviewed obtaining the identification number “NCT05902065.”

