### Sample size estimation

2.2

The sample size was estimated based on the primary outcome of the study “the evaluation of the difference in gait assessed by the Tinetti Performance-Oriented Mobility Assessment gait (POMA-G) scale (36) between the TT+AVR and the TT group at T1.” Data for the estimation were obtained from a previous study aiming to evaluate the effects of non-conventional TT (partial weight-supported TT) on patients with PD (37) using the POMA-G scale. Mean values observed in the POMA-G score after 4 weeks of treatment were 10.7 ± 1.1 and 11.7 ± 0.5, for the conventional gait training and partial weight-supported TT group, respectively, leading to a high effect size *d* = 1.17. Based on those data and assuming a statistical power of 95% and an *α* = 0.05, the resulting sample was 20 subjects per arm. Dropouts are expected to be around 20%. To compensate for possible dropouts, the enrolment of a further 8 patients has been deemed appropriate, reaching an estimate of 24 subjects per group. Thus, 48 patients will be enrolled starting from the date of Ethical Committee approval, within July 2024. The sample size has been estimated using G*Power software (38).

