#### Clinical assessment

2.4.1

Clinical assessment will be performed by raters experienced in PD patients’ evaluation. The Montreal Cognitive Assessment (MoCA) (40) and Beck Depression Inventory II, Italian version (BDI) (41) will be used to exclude patients with dementia and severe depression. All enrolled participants will be assessed by the following scales/tests:

the Performance Oriented Mobility Assessment (POMA) (36) to evaluate gait (POMA-G) and balance (POMA-B)the MDS-UPDRS part III (42, 43) to evaluate different symptoms and signs in PDthe Italian version of the Parkinson’s disease cognitive rating scale (PD-CRS) (44) to evaluate global cognitive functionsthe Trail-Making-Test A and B (TMT-A and B) (45), the Stroop Test (46), and the Symbol Digit Test (SDT) Italian oral version (47) to evaluate attention and executive functionsthe Parkinson’s Disease Questionnaire (PDQ-39-IT) (48) to evaluate the perceived health-related quality of lifethe Modified Parkinson Activity Scale (MPAS) (49) and the TUG test (50) to evaluate functional mobilitythe 6-Minute Walking Test (6MWT) (51) to evaluate walking endurance; the test will be performed indoors along a 30 m corridor, following the American Thoracic Society guidelines (52)the Freezing Of Gait Questionnaire (FOG-Q) (53) to evaluate the frequency and duration of freezing episodesthe Falls Efficacy Scale, Italian version (FES-I) (54) to evaluate the fear of falls in different situations of riskthe fall questionnaire (55) to account for the number of fallsthe Numerical Rating Scale (NRS 0–10) (56) to evaluate current painthe modified Barthel Index (mBI) (57) to evaluate functional independence in the basic activities of daily living

At T1, participants will be also asked to rate their satisfaction with the treatment using a 5 Point Likert Scale (range: 1–5, where 5 indicates a very high appreciation).

To avoid inter-rater variability, participants will be evaluated by the same rater (1–2: Neurologist or Physiatrist; 3–5: Neuropsychologist; 6–12: Physiotherapist) at different time points. All scales will be repeated in the same version, except for MoCA, for whom parallel Italian versions are available (58).

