### Outcome measures

2.6

The primary outcome is the difference in gait performance assessed by the POMA-G scale between the TT+AVR and the TT group at T1. The secondary outcomes are differences in mobility (measured by POMA-G at T2 and POMA-B at T1 and T2), in kinematic gait parameters assessed at T1 and T2, measured by the Optogait system, differences in other motor and non-motor symptoms at T1and T2, patients’ satisfaction, assessed with a 5-point Likert scale, and adherence to the treatment.

Exploratory outcome measures include changes in NfL concentration and change in individual Raman spectra of blood-derived cEVs before and after treatment. The correlation between Raman spectra of blood cEVs and the rehabilitation outcome will be assessed (the biological characterization of patients at T0 analyzing cEVs performed by Raman Spectroscopy will provide numerical scores that will be correlated with motor parameters obtained after treatment to identify prognostic biomarkers of rehabilitation outcome).

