As to the other clinical measures, we chose the MDS-UPDRS part III to assess motor symptoms severity. Then, we selected a set of questionnaires and performance tests according to the “European Physiotherapy Guideline for Parkinson’s Disease” recommendations (68). Since the importance of tracking falls in PD due to their frequency and consequences on everyday activities, fear of falling, and QoL (69–72), we included the fall questionnaire, ensuring to report the number of falls, modality, and related consequences, together with the FES-I questionnaire, to evaluate fear of falling. The incident rate of falls over 6 months after the end of treatment will be compared with those referred to the 6 months before the rehabilitation treatment.

In the same way, FOG is a common (63% of PD patients have FOG) and complex gait disorder in PD that frequently causes falls and falls-related anxiety, both of which lower QoL and functional independence, cause shame and dissatisfaction promoting social stigmatization and disability (73–75). Thus, in order to assess this symptom, we included in the tests’ battery the FOG-Q, the only validated tool available to subjectively assess the severity and frequency of FOG (76).

To assess the level of functional mobility the TUG and the MPAS have been selected according to the literature (77). The TUG has the advantage of testing three anchors of functional mobility (gait, balance, and transfers), and provides also indirect estimation of the risk of falls; however, it assesses the patient’s capacity in a neutral setting, rather than performance in daily living activities. For this reason, we adopted the MPAS, a scale specifically designed to evaluate functional gait, balance and transfers through different scenarios in daily activities. The major limitation of MPAS is the number of accessories, space, and time needed to perform the test which may not be practical or feasible in all centers.

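### Within-group results are given the job of assessing treatment effects in a trial with two active arms, and the ANOVA term that tests treatment is not named

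*Protocol article*

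**What the plan says.** Section 2.7.2 (Data analysis) of the protocol article states the purpose of the outcome analyses: "Both within and between-group analyses will be conducted to assess at each time point the effects of the treatments delivered". This covers primary and secondary outcomes. The next sentence gives the concrete form: "a two-way repeated measures ANOVA will be used with a within-factor (time of assessment) and a between-factor (group". No term of that model is singled out as the test of treatment, and within-group results are not called descriptive. One threshold serves throughout: "For all analyses, statistical significance will be set at *p* < 0.05".

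Other sections fix the question and the setting:
- Section 2.6 (Outcome measures): "The primary outcome is the difference in gait performance assessed by the POMA-G scale between the TT+AVR and the TT group at T1". Section 2.2 sizes the trial on the same contrast.
- Section 2.1 (Study design): the "experimental intervention is represented by an TT+AVR and the comparator by a conventional TT".
- Section 2.4.1 (Clinical assessment): "All scales will be repeated in the same version, except for MoCA". The same rater sees a participant at every time point.
- Sections 2.3 and 2.5: drug therapy is to stay stable until T1.
- Section 3 (Discussion), on falls: "The incident rate of falls over 6 months after the end of treatment will be compared with those referred to the 6 months before" treatment. That sentence names no comparison between arms.

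**The concern.** Randomisation protects the comparison between arms. It does not protect a comparison of an arm with its own past. With no untreated group, a change from T0 can come from several sources besides the training:

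- **Practice.** The cognitive tests other than the MoCA are repeated in identical form.
- **Regression to the mean.** Patients enter because they have a gait disturbance.
- **Expectation.** Raters are blind to allocation, but a rater who sees the same patient each time can tell before from after. The Discussion itself reports that the POMA is open to tester bias.
- **Drug changes.** These matter for T2 only, since therapy must be stable up to T1.

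The article gives no size for any of these, so they are possible contributions and not known ones. They are expected in both randomised arms, so they do not bias the between-group contrast. They do make a within-arm p-value, or the time main effect, unusable as evidence of treatment. At stake is the reading of the results: the present wording would let a gain over time be reported as an effect of training. It would also leave open a claim for AVR based on a significant change in one arm and not in the other.

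**Working it through.** **1. The plan's own figure.** Section 2.2 gives T1 means of 10.7 (SD 1.1) and 11.7 (SD 0.5), power 95% and α = 0.05.
- Pooled SD = √((1.1² + 0.5²)/2) = √0.73 = 0.854.
- d = (11.7 − 10.7)/0.854 = 1.17, as stated.
- A two-sided two-sample t-test (noncentral t) has power 0.939 at 19 per arm and 0.950 at 20 per arm.

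The stated 20 per arm is reproduced. That power belongs to the between-group difference at T1 and to no within-arm test.

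**2. What each ANOVA term tests.** Take T0, T1 and T2 as the three levels of time.
- *Time*: change averaged over both arms. It does not compare the arms.
- *Group*: the arm difference averaged over all visits. With equal expected baselines and differences D1 at T1 and D2 at T2, it estimates (0 + D1 + D2)/3. If D1 = D2 = 1, that is 2/3 of the T1 effect.
- *Interaction*: whether the profiles differ anywhere, on (3 − 1)(2 − 1) = 2 degrees of freedom. It compares the arms but is not the T1 contrast.

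None of the three is the section 2.6 quantity as it stands, so the choice of term matters.

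**3. Per-arm tests compared across arms (conditional).** The plan does not say that this will be done. The calculation shows what would follow if it were.

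Assumptions: both arms have the same true change, changes are normal, and each arm has a two-sided paired t-test at 0.05. The documents give no SD of change, so the standardised change dz (mean change divided by SD of change) is assumed over a range. With p the power of one paired test (noncentral t):
- chance that exactly one arm is significant = 2p(1 − p);
- chance that only TT+AVR is significant = p(1 − p), half of that.

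Results for 20 per arm:

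| dz | p | exactly one arm | only TT+AVR |
|---|---|---|---|
| 0 | 0.050 | 9.5% | 4.8% |
| 0.2 | 0.136 | 23.5% | 11.8% |
| 0.3 | 0.247 | 37.2% | 18.6% |
| 0.45 | 0.480 | 49.9% | 25.0% |
| 0.6 | 0.721 | 40.2% | 20.1% |
| 0.7 | 0.844 | 26.4% | 13.2% |
| 0.8 | 0.924 | 14.1% | 7.1% |
| 1.0 | 0.989 | 2.3% | 1.2% |

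Worked line for dz = 0.2: 2 × 0.136 × 0.864 = 0.235.

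If all 24 enrolled per arm were analysed, the chance that exactly one arm is significant would be 26% at dz = 0.2, 50% at 0.4, 17% at 0.7 and 0.6% at 1.0.

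**4. Check by simulation.** With 40,000 trials at 20 per arm, exactly one arm was significant in 9.6%, 37.3%, 49.5%, 40.2% and 14.1% of trials for dz = 0, 0.3, 0.45, 0.6 and 0.8. In the same data the between-group test of change rejected in 4.9% to 5.1%. Half of the nominal 5%, or 2.5%, is the like-for-like figure for a false result favouring TT+AVR.

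**The case against.** The strongest reply is that the ANOVA sentence defines what within- and between-group analyses mean here. It is one factorial model with a time-by-group term that compares change between arms. The time effect pools both arms, so it cannot be significant in one and not in the other. No paired or per-arm test is named. The primary outcome, the sample size and the stated conclusions are all framed as TT+AVR against TT, and labelling secondary results is detail that an article often leaves to a fuller document.

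Much of this stands. A reader might infer that the right contrast is missing, or that AVR will be judged by setting one arm's p-value against the other's. The documents support neither: the between-group comparison is planned, and no cross-arm reading of p-values is described. A reader might also blame drug changes for a T0 to T1 gain, but therapy must be stable over that interval. Nor may the 50% figure be taken as the risk of a false claim for AVR. It counts both directions, sits at the worst assumed dz, and depends on a procedure that the plan does not name.

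The reply does not remove the point. The article does state a purpose for within-group analyses, and it is to assess treatment effects. The ANOVA sentence does not cure this, because it leaves open which term carries the inference. This is a matter of what the text states, not of detail left out.

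**Conclusion.** The point holds in limited form. Section 2.7.2 gives within-group results an inferential role that two active arms cannot support, and it does not name the model term that tests treatment. The primary comparison is present and its sample size reproduces.

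The numerical size is conditional on per-arm tests being run and compared, on equal true change, and on an assumed dz. Disagreement between arms is common for small to moderate changes and rare at about one SD of change. For a split favouring TT+AVR, the range is about 1% to 25% over dz from 0 to 1.0, against 2.5% for the between-group test. The point about the inferential role needs none of these assumptions, since it follows from the design. It is worth settling before the data are analysed.

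**What to change.** Change both sentences in section 2.7.2, for example:

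> Treatment effects are judged only by the TT+AVR versus TT contrast, at T1 for the primary outcome and at T1 and T2 for secondary outcomes, from a model adjusted for the T0 value where one was collected. Changes within each arm are reported as means with 95% confidence intervals and are descriptive.

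The phrase on availability is needed because the C-Gait test is done only at T1 and T2, and satisfaction is rated only at T1. For consistency, the Discussion sentence on falls should name a comparison between arms, with the before-after rates shown as description.

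The cost is the loss of within-arm p-values and a change to the model sentence, since a T0-adjusted contrast takes the place of an unspecified ANOVA term. No new data are needed, and the sample size of 20 evaluable per arm is already based on the between-group contrast.

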### Assessment and timeline of the study

2.4

The study is comprehensive of clinical, instrumental, and biological assessments that will be performed by blind raters, in the “on” medication status of patients, at the same time of day for each subject. Assessment timing is reported in Figure 1. Clinical, neuropsychological, and instrumental variables such as postural sway and gait analysis will be collected at baseline (T0), at the end of the treatment (T1), and 3 months after the end of treatment (T2). At 6 months after the end of treatment (T3) a phone interview will be performed to verify the occurrence of falls in a relevant time frame. The same assessment protocol will be performed at each time point (T0, T1, T2) with some exceptions: automatic acquisition of gait parameters using C-Mill in C-Gait mode will be collected only at T1 and T2 in a subgroup of cases; at T1, a 5-point Likert scale will also be administered to register patient satisfaction; during the phone interview at T3 only the falls questionnaire will be administered; biological samples will be collected at T0 and T1.

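### The primary outcome is the between-arm POMA-G difference at T1, but the only model specified is a group-by-time repeated-measures ANOVA with no T1 contrast, no deciding term and no baseline adjustment

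*Protocol article*

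**What the plan says.** Section 2.6 (Outcome measures) states: "The primary outcome is the difference in gait performance assessed by the POMA-G scale between the TT+AVR and the TT group at T1". POMA-G at T2 is listed there as secondary.

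Section 2.2 ties the sample size to the same contrast: "The sample size was estimated based on the primary outcome of the study". Its inputs are post-treatment means at a single time point, from a previous study of partial weight-supported treadmill training: "Mean values observed in the POMA-G score after 4 weeks of treatment were 10.7 ± 1.1 and 11.7 ± 0.5", "leading to a high effect size *d* = 1.17". With 95% power and α = 0.05 this gives 20 per arm, raised to 24.

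Section 2.7.2 (Data analysis) covers primary and secondary outcomes together. It first says "Both within and between-group analyses will be conducted to assess at each time point the effects of the treatments delivered". The next sentence, introduced as the specific method, names only the time-by-group ANOVA: "a two-way repeated measures ANOVA will be used with a within-factor (time of assessment) and a between-factor (group").

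The levels of the time factor are not listed there. Section 2.4 gives the schedule: "The same assessment protocol will be performed at each time point (T0, T1, T2) with some exceptions". T3 is a telephone interview about falls only. The one stated use of baseline is descriptive: "The experimental and the control groups will be compared at baseline to explore significant differences in demographic, clinical, and instrumental variables".

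**The concern.** A two-way repeated-measures ANOVA gives two tests that involve treatment, and with three visits neither is a test of the T1 difference.

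- **Group main effect.** This compares the arms on the average of all visits. It includes T0, where randomisation makes the expected difference zero, and T2, which is a secondary time point.
- **Group-by-time interaction.** With three visits it has 2 degrees of freedom and responds to any divergence of profile, including one that appears only at T2.

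Because no term or contrast is named, the test that decides the trial could be chosen after the data are seen. A significant omnibus result could also be reported for the primary outcome without evidence at T1.

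Two further points follow from the model. Baseline POMA-G is collected on everyone but is not used to sharpen the T1 comparison. And conventional repeated-measures ANOVA uses complete cases, so a participant with a T1 value but no T2 value would drop out of the primary analysis.

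**Working it through.** **1. Reproducing the plan's figure.** Inputs from section 2.2: means 10.7 and 11.7, SDs 1.1 and 0.5.

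- Pooled SD = √[(1.1² + 0.5²)/2] = 0.854; d = 1.0/0.854 = 1.17.
- Two-sample t-test (noncentral t), two-sided α = 0.05, power 0.95: n = 20 per arm, power 0.9500. A one-sided test would give 17.

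The stated 20 per arm is therefore reproduced exactly as a two-sided comparison of two means at T1.

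**2. Setting up the comparison.** Take n = 20 per arm, SD 1 at each visit, equal between-visit correlation ρ, and true arm differences of 0 at T0, d at T1 and k·d at T2. The document gives neither ρ nor k; both are assumptions, varied below.

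- Group term: t-test on subject means, with effect d(0 + 1 + k)/3 and SD √[(1 + 2ρ)/3].
- Interaction: F(2, 76), noncentrality (n/2)·Σ(δⱼ − δ̄)²/(1 − ρ), where δⱼ are the three visit differences.
- T1 t-test: effect d, SD 1, 38 df.
- T1 ANCOVA on T0: effect d, residual SD √(1 − ρ²), 37 df.

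Example with d = 1.17, ρ = 0.5, k = 1:

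- Group term: effect 1.17 × 2/3 = 0.78, SD √(2/3) = 0.816, power 83.7%.
- Interaction: Σ = 0.78² + 2 × 0.39² = 0.913, noncentrality 10 × 0.913/0.5 = 18.3, power 97.1%.
- ANCOVA: 1.17/√0.75 = 1.35, power 98.6%.

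**3. Power (%), with T2 keeping 100 / 50 / 0% of the T1 effect.**

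| d | ρ | Group term | Interaction | T1 t-test | T1 ANCOVA |
|---|---|---|---|---|---|
| 1.17 | 0.3 | 90.8 / 69.5 / 37.7 | 89.7 / 78.9 / 89.7 | 95.0 | 96.5 |
| 1.17 | 0.5 | 83.7 / 59.8 / 31.3 | 97.1 / 91.1 / 97.1 | 95.0 | 98.6 |
| 1.17 | 0.7 | 76.7 / 52.2 / 26.9 | 99.9 / 99.1 / 99.9 | 95.0 | 99.9 |
| 0.8 | 0.3 | 61.4 / 39.3 / 20.3 | 57.3 / 45.1 / 57.3 | 69.3 | 73.3 |
| 0.8 | 0.5 | 52.1 / 32.7 / 17.2 | 72.9 / 59.5 / 72.9 | 69.3 | 81.2 |
| 0.8 | 0.7 | 45.2 / 28.1 / 15.1 | 92.2 / 82.5 / 92.2 | 69.3 | 93.2 |

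A simulation of three of these settings (4,000 runs each) agreed within about 1.2 percentage points.

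**4. Does the interaction test T1?** Put no difference at T0 or T1 and 0.8 SD at T2. Then Σ = 0.8² × 2/3 = 0.427, and the noncentrality is 4.27/(1 − ρ), that is 6.1, 8.5 and 14.2 for ρ = 0.3, 0.5 and 0.7. The interaction is significant with probability 57%, 73% and 92%. A T1 test keeps its 5% level, because there is no T1 effect to find.

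**The case against.** **The text may already allow a T1 test.** The sentence before the model promises between-group analyses at every time point. Within a group-by-time ANOVA, the comparison at T1 is a simple effect, close to the t-test that sized the trial. This stands in part. A reader might infer that the primary p-value cannot answer the primary question; the documents do not show that, because they leave the p-value open. But no such contrast is named, and a simple effect would be unadjusted for T0. Nor is this merely detail left to an analysis plan: the article does fix a model for the primary outcome.

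**The time levels are inferred.** Section 2.7.2 does not list them. With T0 and T1 only, the interaction has 1 degree of freedom and tests the difference in change, a valid estimate of the T1 effect under randomisation. At d = 1.17 its power would be 86.1%, 95.0% and 99.6% for ρ = 0.3, 0.5 and 0.7, against 96.5%, 98.6% and 99.9% for ANCOVA. The multi-visit objection would then fall away; the case for adjustment would remain.

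**The interaction is not uniformly weak.** Correct. At d = 1.17 and ρ of 0.5 or more it has at least 91% power. At d = 0.8, ρ = 0.8 and full persistence it reaches 98.7%, against 98.4% for ANCOVA. The low group-term figures matter only if that term decides, which nothing in the text says.

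**The T2-only scenario is unusual.** It is. It shows what the interaction responds to; it is not a forecast.

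**Two inferences to avoid.** The 20% dropout in section 2.2 cannot be read as the loss at T2: section 2.3 ties dropout to missing more than 5 training sessions, and no T2 loss rate is given. The SDs of 1.1 and 0.5 come from another study of different interventions, so they do not show that this trial will breach an equal-variance assumption.

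**Conclusion.** The point holds as a mismatch between the primary outcome and the stated analysis, together with an unused baseline. The outcome and sample size concern one T1 contrast; the model section names neither that contrast nor a deciding term. On a T0/T1/T2 reading, neither standard treatment term of the ANOVA tests it.

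The mismatch is the main fault and loss of power comes second. At the design effect the group term is below the planned 95% in every setting examined. The interaction ranges from clearly below it to above it, depending on correlation and persistence. ANCOVA on T0 is at or above the unadjusted T1 test throughout, with a gain of 4 to 24 points at d = 0.8 (73.3 − 69.3 to 93.2 − 69.3). These sizes rest on assumed ρ of 0.3 to 0.7, equal correlations, equal variances and 20 evaluable per arm. The number of participants with T1 but not T2 cannot be derived from the document.

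**What to change.** In section 2.7.2, name one primary test: ANCOVA of POMA-G at T1 on arm, with POMA-G at T0 as covariate. The equivalent T1 contrast from a baseline-adjusted mixed model would also serve. Report the adjusted mean difference with its 95% CI, and include everyone with a T1 value whether or not T2 was attended. State that the T2 comparison and the group-by-time interaction are secondary.

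Heteroscedasticity-robust standard errors, and a permutation or proportional-odds check for a bounded score, are optional additions.

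The cost is a change of wording, ideally made before any unblinded look at outcome data. T0 POMA-G is already collected, no patients or visits are added, and these models are standard in the statistical software the protocol names.
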